***Study Methods: Follow-Up***

Emails from REDCap will be sent automatically at 3 and 6 months after the baseline visit. We will send up to 3 emails (approximately 7 days apart) with a link to complete follow-up PROMs. If there is not response by approximately 3 days after the third email, a researcher will call the patient up to 3 times to complete the follow-up surveys via telephone.

- Follow-Up Surveys to complete at 3 and 6 months
  - KOOS JR
  - PROMIS Global 10
  - DRS
- Time Windows
  - 3 month follow-up window: 2.75 to 4 months after baseline visit.
  - 6-9 month follow-up window: 5.75 to 10 months after baseline visit.
- For patients for whom Spanish is indicated as the preferred language, the research assistant will call using the interpreter service.
  - To call the interpreter service:
    - Dial [name]
    - Enter 1755794
    - Enter MSKI PIN: 1115
    - Select Language: Spanish
    - Connect & conduct follow-up questionnaires using interpreting service

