***Allocation***

Sequence Generation: REDCap algorithm (see details below)

Concealment: Sequence concealed by REDCap algorithm

Implementation: Research Assistant (see protocol below for Randomization)

Blinding: Unblinded/ no masking

For the randomization, we will stratify by variables known or suspected to be predictive of decision quality and/or treatment choice by using stratified random block randomization. Participants will be stratified by 3 factors: ethnicity (Hispanic/non-Hispanic), insurance (public safety net insurance/other insurance) and attending surgeon. Block randomization will occur within each stratum with random block sizes of 4 and 6, and an equal number of patients assigned to the intervention and control arms within each block. These steps are carried out automatically in the REDCap study database. This strategy ensures that participants are equally distributed to treatment and control through time, therefore controlling for any time varying effects that may occur. The Dell Medical School Biomedical Data Science Hub will oversee the randomization.

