***Recruitment methods: Randomization***

The researcher will then enroll the patient and perform randomization using the REDCap online platform. Patients will be informed if they are in the intervention group (“Full Tool”) or control group (“Edu Only”). Researchers will do their best to follow standard scripts for each step of the recruitment as below.

- Prior to entering the room, the researcher should:
  - Open and log into REDCap
  - Open and log into OM1
- REDCap randomization procedure on clinic iPads, in room with patient:
  - From the REDCap homepage, enter the “Joint Insights” project
  - Go to Add/Edit Records on the left hand side of REDCap, then “Add new record”
  - Complete the “Informed Consent and HIPAA” record, including a signature
  - Complete the **first three items** on the “Enroller: Initial Visit Details” record
    - Site & clinic-associated surgeon ([name] vs [name])
    - Is the patient Hispanic? (Y vs N)
    - What kind of insurance? (MAP/Medicaid vs Other)
  - Click the “Randomization” button, which will show either:
    - “Group A – Full tool”
    - “Group B – Educational materials only”

[figure not shown]

- - Inform the patient as to the group into which they have been randomized
    - *FULL TOOL: “You have been selected to receive the educational materials and the software. Let me briefly talk you through the process. Please kindly read the education material on this iPad at your own pace, answer the questions at the end, and use the sliders to tell us about your preferences and experiences. You will then receive a report customized to you which can guide discussion with your provider. Please feel free to ask any questions during this consultation. Thanks in advance for completing some survey questions on how it all went at the end of the visit, please be sure to wait for me to return before leaving.”*
    - *EDUCATION ONLY: “You have been selected to receive the educational materials. Let me briefly talk you through the process. Please kindly read the education material on this iPad at your own pace. You will then have a chance to discuss your problem and treatment options with your provider. Please feel free to ask any questions during this consultation. Thanks in advance for completing some survey questions on how it all went at the end of the visit, please be sure to wait for me to return before leaving.”*

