      - Click on the “Select OA severity” dropdown menu to select the radiographic severity (KL 3 or 4)
      - Show the results with the patient and explain that they will receive a printed-out version for discussion with their provider
      - Leave the room
      - Print out the score report(s) and hand to the provider or hang in the basket on the exam room door
      - Inform the provider the patient is ready to be seen
      - Write the patient’s “Benefit” percentage under “notes” on the clinic whiteboard
- During the provider consultation
  - Research assistant must record for REDCap:
    - The number of minutes the counseling provider was in the room
      - This includes [name], [name], the Arthroplasty Fellow, Advanced Practice Providers (APPs).
      - As much as possible, the amount of time should only reflect time spent on the shared decision making conversation; this means that time spent on injections does not count, and time spent collecting medical history should not contribute either
      - However, we recognize there is variation in which provider or learner contributes to each part of the visit – for instance a learner (medical student or resident) might collect history for some patients which will *not* be included in the final time calculation, while the APPs might collect history for others and this *will* be included
      - Ultimately, we just record the exact number of minutes any of the above providers who are listed specifically by name spend in the room *except* after they come out to grab an injection and go back in to perform the injection
    - Enter the total consultation minutes into the appropriate field in REDCap
  - If the exact timing is missed, RA will confirm an estimate with the provider

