***Study Methods: Follow-Up Documentation***

- On Box
  - Completion of “Joint Insights Follow-Up Tracker” with the date of each follow-up email or phone call attempt
- On REDCap
  - Completion of relevant surveys for each patient at each appropriate time point
    - Patients contacted by email or text will complete surveys themselves
    - For patients contacted by phone, the researcher will enter the patient’s responses into REDCap
  - If patients decide to withdraw, they should be marked as “Withdrawn” in REDCap
  - If patients are lost to follow-up as indicated in the guidelines above, their follow-up surveys will be left blank in REDCap

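### Telephone follow-up neither separates the caller from the enrolling researcher nor hides the arm, which leaves phone-collected secondary outcomes open to avoidable interviewer bias

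*Protocol*

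**What the plan says.** The *Allocation* section of the protocol states "Blinding: Unblinded/ no masking" and makes no exception for outcome collection. Under *Recruitment methods: Randomization*, "The researcher will then enroll the patient and perform randomization using the REDCap online platform", and one of that person's steps is: "Inform the patient as to the group into which they have been randomized". For Full Tool patients, *Recruitment Methods: OM1 Enrollment & Delivery* adds this step for the same staff: "Show the results with the patient and explain that they will receive a printed-out version for discussion with their provider".

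*Study Methods: Follow-Up* covers KOOS JR, PROMIS Global 10 and DRS. It sends up to three emails with a survey link. If there is no response, "a researcher will call the patient up to 3 times to complete the follow-up surveys via telephone". A separate rule applies by language: "For patients for whom Spanish is indicated as the preferred language, the research assistant will call using the interpreter service". *Recruitment Methods: Baseline Visit Questionnaires* also lets each patient choose phone or email for follow-up.

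*Study Methods: Follow-Up Documentation* says that email and text surveys are self-completed, and then: "For patients contacted by phone, the researcher will enter the patient’s responses into REDCap". According to *Allocation*, randomisation runs in the REDCap study database, where these surveys also sit.

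**The concern.** Patient and provider cannot be masked in this comparison. A person who phones months later to read out a questionnaire can be, at least in part. The protocol makes no such distinction. It does not say that the caller should differ from the enroller, that the allocation should be kept from the caller, or that the calls follow a script, although it does script the baseline visit.

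Decision regret, function and global health are self-reports. A caller who knows the arm, or who delivered the tool, can influence prompting and recording, and a patient may give a more favourable answer to the person who showed them their report. Functional outcomes and decision regret are named under *Objectives*, and *Data Management & Analysis* plans treatment-by-time models for the 3- and 6-9 month data. No analysis can remove this kind of bias once the data are collected.

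**Working it through.** The protocol gives no figure on this point, so the check is first a reading of the procedures and then an illustration on assumed inputs.

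**Who could know the arm**

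| Step | Who | Source (protocol section) |
| --- | --- | --- |
| Randomises in the room and announces the arm | The researcher | *Recruitment methods: Randomization* |
| Sets up the arm-specific module, shows the Full Tool report | The researcher | *Recruitment Methods: OM1 Enrollment & Delivery* |
| Phones the patient | A researcher, or the research assistant with an interpreter | *Study Methods: Follow-Up* |
| Enters phone answers | The researcher | *Study Methods: Follow-Up Documentation* |

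*Administrative Information* lists two people under recruitment, and both also appear under implementation and operations. Overlap between enroller and caller is therefore plausible, but it is not stated.

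**Which outcomes are exposed**

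- Exposed: DRS, KOOS JR and PROMIS Global 10, when completed by phone.
- Not exposed: the same instruments completed by email or text, where there is no interviewer.
- Not exposed: the primary analysis. Its response is the DQI score (*Data Management & Analysis*), which patients complete at the end of the visit (*Recruitment Methods: Baseline Visit Questionnaires*).

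**Illustration of size**

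Let p be the share of surveys done by phone and b the shift in the between-arm difference, in SD, within those surveys. Neither is in the protocol. Assumed ranges are p = 0.2 to 0.6 and b = 0.1 to 0.3.

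1. Overall shift: d = p × b. Lowest: 0.2 × 0.1 = 0.02 SD. Highest: 0.6 × 0.3 = 0.18 SD. With b = 0.2 the range is 0.2 × 0.2 = 0.04 to 0.6 × 0.2 = 0.12 SD.
2. Standard error of the arm difference with 90 per arm (the protocol's 200 enrolled less 10% loss is 180): SE = √(2/90) = 0.149 SD.
3. Two-sided rejection rate at nominal 5% when there is no true effect, using a simple two-sample normal approximation at one time point: 1 − Φ(1.96 − d/SE) + Φ(−1.96 − d/SE). For d = 0.18, d/SE = 1.207, and the rate is 1 − Φ(0.753) + Φ(−3.167) = 0.227.

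| Phone share p | b = 0.1 | b = 0.2 | b = 0.3 |
| --- | --- | --- | --- |
| 0.2 | 0.02 SD; 5.2% | 0.04 SD; 5.8% | 0.06 SD; 6.9% |
| 0.4 | 0.04 SD; 5.8% | 0.08 SD; 8.4% | 0.12 SD; 12.7% |
| 0.6 | 0.06 SD; 6.9% | 0.12 SD; 12.7% | 0.18 SD; 22.7% |

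The low end is negligible and the high end is not. The table shows what such a bias could do; it does not show that one exists.

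**The case against.** The trial is openly declared open-label, the instruments are standard questionnaires, and self-completion is the default for patients who choose email. Call assignment and scripts could sit in operating documents. Patients know their arm, so response bias persists whoever calls. All of this is fair, and it limits the point to a modest improvement. It does not remove it: who calls, and what they know, is trial conduct that this protocol already describes, and the caller's contribution can be reduced even though the patient's cannot.

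A reader might infer more than the protocol supports in four ways:

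- *That callers know the arm.* No section says so. It is a possibility left open by the lack of masking, the shared database and the researcher's role at enrolment. The follow-up tracker is described as recording dates of contact attempts, and nothing says that it shows the arm.
- *That every email non-responder and Spanish-preferring patient is fully exposed.* Only non-responders who are reached within three calls supply data; surveys of those lost to follow-up stay blank. Spanish-language calls go through an interpreter, who is not said to know the allocation.
- *That the bias certainly favours the intervention.* Both arms receive an educational module from the same staff, so the wish to please is not confined to one arm. It may be stronger in the Full Tool arm, but that is conjecture.
- *That a REDCap access role would mask the existing recruiters.* They must use the randomisation screen to enrol, and a Full Tool patient's benefit percentage is written on the clinic whiteboard, so a colleague may learn the arm there.

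The illustrated shift with b = 0.2 (0.04 to 0.12 SD) is also smaller than one standard error (0.149 SD).

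**Conclusion.** The point holds as a limited one. DRS, KOOS JR and PROMIS Global 10 answers taken by phone at 3 and 6-9 months are open to interviewer bias that the protocol does nothing to reduce. The size and direction are unknown; favouring the intervention is plausible but not shown. The range of 0.02 to 0.18 SD, with a rejection rate of about 5.2% to 22.7% under no true effect, rests wholly on the assumed phone share (20% to 60%) and assumed shift (0.1 to 0.3 SD), with 90 per arm.

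The primary conclusion on the DQI is not touched by this route, and neither is the sample size, which is built on the DQI. This is an inexpensive improvement to secondary outcomes that the trial names as objectives and plans to model formally.

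**What to change.** Keep patient and provider open-label. Amend *Allocation*, *Study Methods: Follow-Up* and *Study Methods: Follow-Up Documentation* to say that:

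- follow-up calls are made, where possible, by a team member who did not enrol that patient;
- the caller reads a fixed script, and does not look up the arm or ask about it;
- phone answers are entered through the survey link or a form that does not display the randomisation field;
- the mode of completion (email or text, or phone) is recorded for each survey, so that results can be examined by mode.

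The cost is a call-assignment rule, a short script and one extra data field. No additional staff are needed, since the two recruiters can call each other's patients, at some inconvenience in scheduling. Masking will be incomplete, because a recruiter may learn the arm in clinic or from the patient. The change separates the caller from the person who delivered the tool; it does not guarantee a blinded assessor, and it leaves the patient's own response bias in place.

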***Study Methods: Follow-Up Documentation***

- On Box
  - Completion of “Joint Insights Follow-Up Tracker” with the date of each follow-up email or phone call attempt
- On REDCap
  - Completion of relevant surveys for each patient at each appropriate time point
    - Patients contacted by email or text will complete surveys themselves
    - For patients contacted by phone, the researcher will enter the patient’s responses into REDCap
  - If patients decide to withdraw, they should be marked as “Withdrawn” in REDCap
  - If patients are lost to follow-up as indicated in the guidelines above, their follow-up surveys will be left blank in REDCap

***Reasons for Ineligibility or Withdrawal***

Patients are ineligible for the study if any of the following comes to light at any point during the baseline visit or follow-up visits:

- Patient declined
- Screening failure
- Patient withdrawal
- PI withdrawal of patient
  - Reasons:
    - Patient or provider determination that pt. does not have OA
    - Patient had a prior TKA or prior discussion with orthopaedic surgeon about TKA
    - Patient was being considered for revision joint replacement
    - Patient seeking care for trauma condition
    - Non-English or Non-Spanish speakers
    - Patients with BMI below 20 or above 46
    - Age under 45 or over 89
    - Participant unable to give informed consent / issue with cognitive status
    - Other

All patients withdrawing from the study must be marked as “Lost to Follow-Up” in REDCap.

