**Data Management & Analysis**

Data collection at baseline and follow-up will be conducted as above in “Methods” section.

Data management will be conducted using REDCap as detailed above. This is a confidential and secure database protected on UT servers.

Formal comparative analysis will follow the intent-to-treat principle. Primary analysis will compare the intervention and control groups by using multiple linear regression analysis. The model will include DQI score as the response variable and, as explanatory variables, a binary indicator for the intervention group and 7 binary indicator variables representing the 8 strata in order to reflect the stratified randomization design. Additionally, as a secondary analysis, we will compare treatment decisions between the intervention and control groups by using multiple logistic regression. The model will include the treatment decision as the binary response variable and the same explanatory variables as in the linear regression model. Depending on the uptake of the intervention, additional analyses will follow the “per-protocol” principle wherein the main treatment variable will be whether the Joint Insights tool was used.

For analysis of the 3- and 6-9 month data, we will fit linear mixed models for continuous outcomes35 and generalized estimating equations logistic regression models for binary outcomes36, including indicator variables for time point, for treatment group, and for the interaction between the two (yielding treatment effects at 3 months and at 6-9 months). Owing to the balanced design, it will be possible to fit an unstructured correlation model to eliminate any sensitivity to correlation model misspecification.

Data monitoring is not required for this study. No interim analysis is planned.

This is a minimal-risk study. Although we don’t anticipate any adverse events, any adverse events will be reported to the local IRB.

The datasets used and/or analyzed during the current study are available from the corresponding author on reasonable request.

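### Randomised patients can be declared ineligible or withdrawn by the PI at any later visit with the arm known, nothing says they are retained, and two sections code withdrawals differently

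*Protocol*

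**What the plan says.** Under Recruitment methods: Eligibility Screening, the researcher confirms every inclusion and exclusion criterion after imaging and check-in, before approaching the patient. Consent and REDCap randomisation follow.

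Under Reasons for Ineligibility or Withdrawal the window is much wider: "Patients are ineligible for the study if any of the following comes to light at any point during the baseline visit or follow-up visits". The list below that sentence mixes pre-randomisation outcomes (declined, screening failure) with patient withdrawal and "PI withdrawal of patient". The reasons given for the PI's action include "Patient or provider determination that pt. does not have OA", several exclusion criteria, inability to consent, and an undefined Other.

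The Allocation section describes masking as "Unblinded/ no masking", and the randomisation procedure tells the researcher to "Inform the patient as to the group into which they have been randomized".

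Data Management & Analysis says: "Formal comparative analysis will follow the intent-to-treat principle".

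On coding, Study Methods: Follow-Up Documentation says "If patients decide to withdraw, they should be marked as" Withdrawn. Reasons for Ineligibility or Withdrawal says "All patients withdrawing from the study must be marked as" Lost to Follow-Up. Both refer to REDCap.

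**The concern.** Intent-to-treat protects the comparison only if everyone randomised is followed and analysed in the assigned arm. Here a patient can be reclassified as ineligible after the arm is known, after the tool has been used, after the consultation, and even months later. Some of the grounds are judgements (no OA, cognitive status, Other) made by people who know the arm. If removals differ by arm and relate to prognosis or treatment preference, the arms are no longer comparable.

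The most exposed outcomes are those that depend on what happens after the visit: arthroplasty rate, concordance (which uses TKA within 9 months), and KOOS JR, PROMIS Global 10 and decision regret at 3 and 6-9 months. The coding conflict adds to this. If PI removals and patient withdrawals carry the same label, or are labelled inconsistently between staff, an imbalance in PI removals could go unnoticed and participant flow could not be reported reliably.

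**Working it through.** **Text check**

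1. *Does the rule reach past randomisation?* Yes. Eligibility is confirmed before approach and randomisation follows consent at the baseline visit. A rule that names follow-up visits therefore cannot be confined to screening.
2. *Is the judgement made with the arm known?* Yes. There is no masking and the patient is told the arm.
3. *Does any section retain these patients?* No. The intent-to-treat sentence is general, and no section says that a patient declared ineligible stays in follow-up or in the analysis.
4. *Which outcomes are exposed?* The DQI is completed at the end of the baseline visit, after the consultation. Removal before that point can lose it. Removal later cannot, unless collected data are discarded, and no section says they are. TKA status comes from the Athena record and needs no survey, so losing it would be avoidable.
5. *Do the codes agree?* No. The same event is to be coded Withdrawn in one section and Lost to Follow-Up in another.

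**The plan's own figure**

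The Sample Size section needs 180 evaluable patients and allows 10% loss: 180 / (1 − 0.10) = 200, which reproduces its target. For d = 0.5, power 0.90 and two-sided 0.05 (sidedness is not stated), the normal formula gives 85 per arm and the t-based calculation 86. The planned 90 per arm is therefore slightly conservative, with t-based power 0.915. The 10% allowance is described as loss to follow-up and makes no separate provision for PI removals.

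**Illustrations of size (removal counts are assumptions; the documents give none)**

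*Surgery rate.* Assume 100 patients in an arm, 40 TKAs, and k removed from that arm only, none of whom has surgery.
- k = 5: 40/95 = 42.1%, a shift of 2.1 percentage points.
- k = 8: 40/92 = 43.5%, a shift of 3.5 points.
- For scale, the standard error of a difference at 40% with 100 per arm is √(0.24/100 + 0.24/100) = 0.069. These shifts are about 0.3 and 0.5 standard errors.

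*Mean of a continuous score.* If the k removed lie g SD below the arm mean, the remaining mean rises by k·g/(100 − k).
- k = 5: 5 × 0.5/95 = 0.026 SD to 5 × 1/95 = 0.053 SD.
- k = 8: 8 × 0.5/92 = 0.043 SD to 8 × 1/92 = 0.087 SD.
- With 90 per arm the standard error is √(2/90) = 0.149 SD, so the largest of these is about 0.6 standard errors.

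*Type I error.* This was simulated with no true effect, 100 per arm, a two-sample t-test and 6,000 runs. The lowest patients on a factor correlated with the outcome at ρ were removed from one arm only.

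| Removed from one arm | ρ | Shift (SD) | Type I error |
| --- | --- | --- | --- |
| 5% | 0.3 | 0.03 | 0.056 |
| 5% | 1.0 | 0.11 | 0.134 |
| 10% | 0.3 | 0.06 | 0.071 |
| 10% | 1.0 | 0.19 | 0.297 |

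The ρ = 1.0 rows are a worst case.

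*Power.* If 10% are already lost (90 per arm) and a further 5, 10, 15 or 20% are removed from both arms, 86, 81, 76 or 72 per arm remain, and power is 0.903, 0.885, 0.865 or 0.846.

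**The case against.** The strongest defence is that the ineligibility section never says that anyone leaves the analysis. It is a combined status list, part of it plainly pre-randomisation. The only sentence that governs analysis says intent-to-treat, and a statistical analysis plan not shown may retain these patients. This stands to the extent that a reader might infer that the protocol orders exclusion from the analysis, and it does not. The wording problem remains, because an analysis plan cannot recover follow-up that was never collected or separate reasons that were coded alike.

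A reader might also infer that the Full Tool report, which displays OA severity, would drive arm-dependent findings of no OA. The documents do not support that route. Severity is a value that the research assistant selects (K-L 3 or 4), not a test for OA, and both arms must meet the same radiographic criterion before approach. The general open-label concern does not depend on it.

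Most of the listed reasons (prior TKA, age, BMI, language) are facts fixed or measured before randomisation. That is fair, although whether they are detected afterwards could still differ by arm. No OA, cognitive status and Other are the clearly judgement-based items.

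A reader might infer direct bias in the primary DQI comparison. That follows only on the two conditions set out in the working.

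Finally, it goes too far to say that non-response cannot be identified. Non-responders' surveys are left blank and the Follow-Up Tracker on Box logs contact attempts, so non-response is probably traceable. What cannot be told apart reliably in REDCap is PI removal and patient withdrawal.

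**Conclusion.** The concern holds in a limited form. The protocol permits unmasked, partly discretionary removal of randomised patients at any later visit and does not say that they are retained. That conflicts with its intent-to-treat principle for treatment choice, concordance and the 3- and 6-9-month outcomes, and for the DQI only in the two circumstances described. The coding instructions contradict each other outright.

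The size is unknown. With 5 to 8 removals per 100 in one arm, the illustrated shifts are 2.1 to 3.5 percentage points in surgery rate and 0.03 to 0.09 SD in a mean score, against a design effect of 0.5 SD. These figures rest on one-arm removal, no surgery among those removed, an assumed 40% rate and an assumed gap of 0.5 to 1 SD. They show modest bias if removals are few and do not show that bias will occur. The case for changing the text is that it is cheap, and that data not collected after a removal cannot be restored later.

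**What to change.** 1. Limit the eligibility-based and Other removals by the PI to the period before the REDCap randomisation step.
2. State that patients found ineligible afterwards stay in their assigned arm for the intent-to-treat analysis, with surveys and chart-based TKA ascertainment continued. Allow a sensitivity analysis that excludes those ineligible on facts that predate randomisation.
3. Keep the patient's right to leave at any point, as the Interventions section provides. The time limit in item 1 must not apply to patient withdrawal.
4. Handle a participant found unable to give informed consent separately, as a consent matter. Automatic retention should not cover this case.
5. Reconcile the two coding instructions into one set of REDCap statuses: patient withdrawal, PI withdrawal with reason, found ineligible but retained, and lost to follow-up.
6. Because the protocol lists the trial as already enrolling, recode existing withdrawals to the new statuses and tabulate them by arm.

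The cost is protocol wording, a REDCap status field and a short recoding exercise. The downside is that a few truly ineligible patients remain in the analysis and may slightly dilute the effect; the sensitivity analysis shows by how much.
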